### Outcomes

Measuring the impact of knowledge transfer and exchange (KTE) interventions, such as the evidence service proposed here, poses significant challenges as there is a long chain of factors between a KTE intervention such as SHARE and the health status of clients of CBOs or of broader populations [10,35]. For example, it has been demonstrated that assessing the impact of KTE interventions on the practice of physicians poses challenges due to the fact that many factors other than the practice guidelines or recommendations that were disseminated may influence how practices are changed [36-38].

Given these constraints, our primary and secondary outcomes for the trial are proxy measures for research use. The primary outcome will be a measure of utilization that is similar to what Haynes *et al*. (2006) used in their trial of the McMaster Premium Literature Updating Service (PLUS) [39]. Specifically, we will track utilization at the organizational level by calculating the mean number of logins/month/organization (the total organizational logins/month will be averaged across the number of users from each organization) across trial groups during each of the baseline period, intervention period, and crossover period. We will also provide related descriptive measures such as the mean number of logins/month for different types of positions within the organization (executive director, management and staff), the range of logins/month within the organization, the proportion of organizations with at least one user accessing the 'full serve' and 'self-serve' versions of SHARE each month, the frequency with which systematic review records and related resources are accessed (*e.g.*, URLs to abstracts, user-friendly summaries, and/or full-text), and the number of times the email updates to the 'full-serve' group are forwarded.

Each version of the evidence service will be hosted on the Ontario HIV Treatment Network server and for the duration of the trial will require a user login that will be used to link each participant's identification with their usage of the evidence service website and to their organization. SHARE is a new database that is not yet publicly available (it will be upon completion of the trial), which allows us to evaluate it without participants being able to gain access from a publicly available site. In addition, requiring a user login will help protect against contamination of the intervention and control group. However, we cannot protect fully against the possibility of participants from the organizations sharing information given that many may collaborate with each other.

For the secondary outcome, we will use the theory of planned behaviour to measure participants' intention to use research. The theory of planned behaviour proposes a model about how human action is guided [40,41] and consists of three variables -- attitudes (*i.e.*, beliefs and judgments), subjective norms (*i.e.*, normative beliefs and judgments about those beliefs), and perceived behavioural control (*i.e.*, the perceived ability to enact the behaviour) -- that shape the behaviour intentions of people, which is subsequently a strong predictor of future behaviour [41-43]. In Figure 1, we outline the model of the theory of planned behaviour and map how different elements of the evidence service may affect each of the three variables.

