**Methods/design:**

We will conduct a two-arm randomized controlled trial (RCT), along with a follow-up qualitative process study to explore the findings in greater depth. All CBOs affiliated with Canadian AIDS Society (n = 120) will be invited to participate and will be randomized to receive either the 'full-serve' version of SHARE or the 'self-serve' version (a listing of relevant systematic reviews with links to records on PubMed and worksheets that help CBOs find and use research evidence) using a simple randomized design. All management and staff from each organization will be provided access to the version of SHARE that their organization is allocated to. The trial duration will be 10 months (two-month baseline period, six-month intervention period, and two month crossover period), the primary outcome measure will be the mean number of logins/month/organization (averaged across the number of users from each organization) between baseline and the end of the intervention period. The secondary outcome will be intention to use research evidence as measured by a survey administered to one key decision maker from each organization. For the qualitative study, one key organizational decision maker from 15 organizations in each trial arm (n = 30) will be purposively sampled. One-on-one semi-structured interviews will be conducted by telephone on their views about and their experiences with the evidence service they received, how helpful it was in their work, why it was helpful (or not helpful), what aspects were most and least helpful and why, and recommendations for next steps.

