## Methods/design

We will conduct this trial using a sequential explanatory mixed methods design [25], beginning with the two-arm randomized controlled trial (RCT), and then following up with a qualitative process study to explore the RCT findings in greater depth. The trial will run for 10 months, which includes a two-month baseline period where all participants receive the 'self-serve' evidence service, a six-month period where the intervention group will receive the 'full-serve' evidence service and the control group will continue to receive the 'self-serve' evidence service, and a final two-month period where both groups will receive the 'full-serve' version of SHARE.

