### Data management and analysis

Data will be entered into SPSS 16.0 using unique identifiers that link each participant to their respective organizational identifier assigned during the randomization process. Analyses will be conducted by two members of the team ([name] and TB) and, during the analysis, all investigators -- except for one of us who is involved in the both the analysis and randomization (TB) -- will be blinded to the key linking the organizations to their unique identifiers.

We will treat both outcome measures as continuous variables and analyze the change in these measures over time using a two-way mixed effects linear repeated measures analysis of variance (ANOVA), which will assess the effects within groups, between groups, and over time with the latter as the main feature of interest. In addition, we will control for four variables -- province the organization is located in, size of organization (as measured by number full-time equivalent staff in the organization), number of participants that participated from each organization, and the number of clients served each year by the organization -- using analysis of covariance. For the analysis of the secondary outcome, we will also control for whether the key decision maker is full-time or part-time, and whether they have had research training in the past. Each of these variables may at least partially explain research use (*e.g.*, the amount of staff support an executive director or manager has may determine the extent to which they can spend time finding and using research evidence), and therefore adjusting for them will allow for a better assessment of the effects of the intervention. Moreover, as part of a secondary analysis, we will assess whether there is an interaction between each (entered as fixed factors) and the outcome measures. Given the likelihood that the distribution of the outcomes will be skewed, we will transform the data where necessary and possible, which may include adjusting the time period for which we calculate the mean number of logins/month/organization (*e.g.*, calculating the mean over two months) if the number of logins is low and there are insufficient data for analysis. We will also qualitatively compare the number of participants in the intervention and control groups that do not complete the follow-up survey, and attempt to assess if there are reasons for why they dropped out based on their baseline characteristics.

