### Statistical precision

Given a fixed sample size of approximately 85 organizations (70% of 120 organizations) a sample size calculation is not relevant. Instead, we have calculated the level of statistical precision that we can expect given our fixed sample size. To calculate the expected statistical precision in the trial, an estimation of intra-class correlation coefficient (ICC) of measurements for individuals over time for the primary outcome is required. However, we have no mechanism to estimate the ICC due to the fact that no similar study with this population has been conducted (at least to our knowledge). Therefore, we calculated estimates of statistical precision for ICCs of 0.2, 0.3, 0.5, 0.7 and 0.8 based on a six-month trial period with 80% power, an estimated standard deviation of 1.0, significance of 0.05 (two-sided test), and 42 organizations per study group (total n = 85) [50]. Assuming the primary outcome data will be collected from all 85 organizations during the intervention period at six follow-up points (one per month), the time-averaged detectible differences (in standard deviation units) between the two groups is at best 0.35 (for ICC = 0.2), which increases with successively greater ICCs to 0.39 (for ICC = 0.3), 0.47 (for ICC = 0.5), 0.53 (for ICC = 0.7), and 0.56 (for ICC = 0.8).

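### The primary outcome has no single time frame or arm contrast, and the listed periods include crossover months in which both arms have full-serve

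*Protocol article*

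**What the plan says.** Four places in the protocol article describe the primary outcome or its analysis.

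- **Abstract, Methods/design:** mean logins per month per organization "between baseline and the end of the intervention period", which is months 1 to 8 of the 10-month trial.
- **Outcomes:** the same measure is calculated "across trial groups during each of the baseline period, intervention period, and crossover period", which covers months 1 to 10 in three blocks.
- **Data management and analysis:** the team will "analyze the change in these measures over time using a two-way mixed effects linear repeated measures analysis of variance (ANOVA"). Effects within groups, between groups and over time are listed, and the over-time effect is given most weight. No period is left out, and no term is named as the arm comparison that decides the trial.
- **Statistical precision:** the detectable differences are time-averaged differences between the groups, from data collected "during the intervention period at six follow-up points (one per month"), which is months 3 to 8.

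The main Methods/design section sets the schedule. Both arms have self-serve in months 1-2. The arms differ in months 3-8. Then comes "a final two-month period where both groups will receive the 'full-serve' version of SHARE", months 9-10.

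**The concern.** The arms receive different services in only six of the ten months. Any primary term that averages over the other four months mixes the treatment contrast with months in which none is expected, and this pulls the estimate towards zero. Any baseline-versus-later term that counts months 9-10 as follow-up does the same.

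The four descriptions allow several primary analyses: a months 3-8 level difference, a change from baseline, a three-period interaction, or a between-groups term over all periods. These estimate different quantities with different precision, and only the first matches the published detectable differences. The analysis section also lets the averaging period for logins be adjusted if counts are low. With window and contrast open as well, the primary result could be chosen after the logins are seen, or a real effect could be reported as none.

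**Working it through.** **Inputs from Statistical precision.** 42 organizations per group; "based on a six-month trial period with 80% power"; "significance of 0.05 (two-sided test"); "an estimated standard deviation of 1.0"; six monthly measures; ICC over time of 0.2, 0.3, 0.5, 0.7 and 0.8.

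**Assumptions added here.** Exchangeable correlation, constant SD, a constant effect d in months 3-8, no arm difference in months 1-2 or 9-10, and a normal approximation.

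**Step 1: reproduce the published figures.** The variance of an organization's mean over m months is V(m) = (1 + (m−1)·ICC)/m, and the detectable difference is (1.960 + 0.842)·√(2·V(m)/42).

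- At m = 6 and ICC 0.2, V = 2.0/6 = 0.333, and 2.8016·√(0.6667/42) = 0.353.
- Across the five ICCs the results are 0.353, 0.395, 0.467, 0.529 and 0.558, against the stated 0.35, 0.39, 0.47, 0.53 and 0.56. Power at the stated values is 79.3%, 79.1%, 80.5%, 80.1% and 80.3%.
- At ICC 0.2, m = 8 would give 0.335 and m = 10 would give 0.323. Neither fits, so the calculation used the six intervention months alone.

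**Step 2: keep those differences as the true d and change only the term tested.** For the one-degree-of-freedom terms, power is Φ(effect/SE − 1.960), with SE = √(2·V/42).

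- *(a) Between groups, months 1-10 averaged:* effect 6/10·d, V(10) = (1 + 9·ICC)/10. At ICC 0.2: 0.210/√(2·0.280/42) = 0.210/0.1155 = 1.82, power 44%.
- *(b) Between groups, three period means weighted equally:* effect d/3, V = ICC + (1−ICC)(1/2 + 1/6 + 1/2)/9. At ICC 0.2: V = 0.304, 0.1167/0.1203 = 0.97, power 16%.
- *(c) Group-by-period test, three periods, 2 df:* noncentrality (42/2)·d²·(2·0.6² + 6·0.4² + 2·0.6²)/(1−ICC) = 50.4·d²/(1−ICC). At ICC 0.2: 50.4·0.1225/0.8 = 7.72, power 70%.
- *(d) Simple change, months 1-2 mean to months 3-8 mean:* effect d, V = (1−ICC)(1/6 + 1/2). At ICC 0.2: 0.35/√(2·0.533/42) = 0.35/0.1594 = 2.20, power 59%.
- *(e) Months 3-8 mean adjusted for months 1-2 mean:* effect d, V = V(6) − ICC²/V(2), with V(2) = (1 + ICC)/2. At ICC 0.2: V = 0.333 − 0.04/0.6 = 0.267, 0.35/0.1127 = 3.11, power 87%.

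| ICC | d (SD) | (a) months 1-10 | (b) three period means | (c) interaction | (d) simple change | (e) months 3-8, baseline-adjusted |
|---|---|---|---|---|---|---|
| 0.2 | 0.35 | 44% | 16% | 70% | 59% | 87% |
| 0.3 | 0.39 | 42% | 16% | 85% | 74% | 92% |
| 0.5 | 0.47 | 41% | 16% | 99% | 96% | 99% |
| 0.7 | 0.53 | 40% | 16% | >99% | >99% | >99% |
| 0.8 | 0.56 | 40% | 16% | >99% | >99% | >99% |

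At ICC 0.2, the same true effect has between 16% and 87% power depending on a choice the protocol leaves open. The low-ICC shortfall in (d) has nothing to do with crossover. It comes from subtracting a noisy two-month baseline.

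**The case against.** A reader might infer that the protocol pools the crossover months into the arm comparison, so that the difference is diluted and the stated 80% power is lost. The text does not support that.

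- The Outcomes wording gives a separate mean for each period, not one mean over ten months, and reporting crossover use separately dilutes nothing.
- The abstract stops before crossover.
- The analysis section gives most weight to effects over time. A three-period interaction falls below 80% only at ICC 0.2.
- The precision figures are right for what they describe. The 80% is an input to detectable differences for a fixed sample, not a guarantee for a target effect, and the section itself says a sample size calculation is not relevant.
- This is a condensed article, and the months entering a model are often left to an analysis plan.

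The first four points stand, and they make the power losses conditional. The last does not remove the issue. The article itself states an outcome, a model and a precision calculation, and these do not describe the same quantity. Separate period means do not protect the between-groups term either: if the three means are its levels, that term estimates d/3. Only a named contrast or interaction protects the comparison, and none is named.

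**Conclusion.** The concern holds as an inconsistency in the time frame and arm contrast of the primary outcome. The abstract, Outcomes, Data management and analysis, and Statistical precision do not fix one quantity, and one of the listed periods has no treatment contrast. Statistical precision is correct for a months 3-8 level difference, but the analysis section does not specify that test.

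The size depends on the term used. At the published detectable differences, power would be about 40-44% or about 16% for a between-groups term that includes all periods. It would be 70% at ICC 0.2 for the three-period interaction, and 59% and 74% at ICC 0.2 and 0.3 for simple change. From ICC 0.5 upwards, the interaction and the change score both have at least 96%. All of this rests on exchangeable correlation, constant SD, a steady effect in months 3-8 and no arm difference elsewhere. It does not show that the trial as planned has lost its power.

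**What to change.** Bring the abstract, Outcomes, and Data management and analysis into line with Statistical precision:

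- State the primary contrast as the between-arm difference in mean logins per user per month over months 3-8.
- Use months 1-2 only as a baseline covariate.
- Leave months 9-10 out of the primary model, and report them separately and descriptively.

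Under the assumptions above, this contrast has at least 87% power at the published differences for every listed ICC, and it removes the choice of window. The cost is wording changes in three places and one restriction in the analysis code, with no new data.

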**Figure 1 F1:**
[figure not shown]
**Linkages among the intervention, contextual developments, and theory of planned behaviour constructs**.

The theory of planned behaviour has been extensively used and tested in the fields of psychology and healthcare. Systematic reviews conducted in the psychology field have demonstrated that the theory explains about 39% of the variance in intention and about 27% of the variance in behaviour [42,43]. A number of studies have demonstrated the feasibility of producing valid and reliable measures of the key theory of planned behaviour constructs for use with healthcare professionals [44-46]. A systematic review suggests that the proportion of the variance in healthcare professionals' behaviour explained by intention was similar in magnitude to that found in the broader literature [47]. With the successful transfer of the theory from assessments of individuals to assessments of healthcare professionals involved in an agency relationship with their patients, we are confident in its further transfer to key decision makers in CBOs in agency relationships with other decision makers and staff in their organization.

Using a manual to support health researchers who want to construct measures based on the theory [41], our colleagues have developed and sought preliminary feedback on a data-collection instrument by first assessing face validity through interviews with key informants and then pilot testing it with 28 policymakers and researchers from 20 low- and middle-income countries who completed it after participating in a KT intervention [48]. In addition, Boyko *et al*. (2010) found moderate test-retest reliability of the instrument using Generalizability Theory (G = 0.50) [49] when scores from a sample of 37 health system policymakers, managers, professionals, citizens/consumers, and researchers participating in stakeholder dialogues convened by the McMaster Health Forum were generalized across a single administration, and even stronger reliability (G = 0.9) when scores were generalized across the average of two administrations of the tool [48]. In the reliability assessment by Boyko *et al*. (2010), the first administration of the tool immediately followed a McMaster Health Forum stakeholder dialogue, which may have promoted enthusiasm for using research evidence among participants. This likely produced higher measures of intention on the first administration of the tool as compared to the second, resulting in the lower G-score. Given that we won't be administering the tool in a similar atmosphere of enthusiasm for using research evidence, it is likely that the level of reliability of the tool will be sufficient without two administrations at both baseline and follow-up.

We have slightly modified the wording in each of the questions of the tool to reflect the different intervention being tested (SHARE) and the target audience (CBOs) (see Additional file 3: Appendix 3). We will administer the instrument to one key decision maker from each organization during the baseline period, as well as at the end of the six-month intervention period, through a brief online survey that takes approximately 10 minutes to complete. We will use unique identifiers for each participant to ensure their responses to the previous survey are linked for calculations of before-and-after changes in their intention to use research evidence. We will follow up with participants who do not complete the survey once per week for three weeks to minimize the number of participants lost to follow up.

### Data management and analysis

Data will be entered into SPSS 16.0 using unique identifiers that link each participant to their respective organizational identifier assigned during the randomization process. Analyses will be conducted by two members of the team ([name] and TB) and, during the analysis, all investigators -- except for one of us who is involved in the both the analysis and randomization (TB) -- will be blinded to the key linking the organizations to their unique identifiers.

We will treat both outcome measures as continuous variables and analyze the change in these measures over time using a two-way mixed effects linear repeated measures analysis of variance (ANOVA), which will assess the effects within groups, between groups, and over time with the latter as the main feature of interest. In addition, we will control for four variables -- province the organization is located in, size of organization (as measured by number full-time equivalent staff in the organization), number of participants that participated from each organization, and the number of clients served each year by the organization -- using analysis of covariance. For the analysis of the secondary outcome, we will also control for whether the key decision maker is full-time or part-time, and whether they have had research training in the past. Each of these variables may at least partially explain research use (*e.g.*, the amount of staff support an executive director or manager has may determine the extent to which they can spend time finding and using research evidence), and therefore adjusting for them will allow for a better assessment of the effects of the intervention. Moreover, as part of a secondary analysis, we will assess whether there is an interaction between each (entered as fixed factors) and the outcome measures. Given the likelihood that the distribution of the outcomes will be skewed, we will transform the data where necessary and possible, which may include adjusting the time period for which we calculate the mean number of logins/month/organization (*e.g.*, calculating the mean over two months) if the number of logins is low and there are insufficient data for analysis. We will also qualitatively compare the number of participants in the intervention and control groups that do not complete the follow-up survey, and attempt to assess if there are reasons for why they dropped out based on their baseline characteristics.

For all analyses, we will use the intention to treat principle, report 95% confidence intervals, and consider p-values equal to or less than 0.05 (two-tailed) to be significant. For the primary outcome measure (mean logins/month/organization), missing data are irrelevant as they are a naturalistic measure. For the secondary outcome measure (obtained through the survey), missing data can be taken into account through the use of a mixed-effects model.

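### The plan analyses change in monthly logins by repeated measures ANOVA without fixing the time unit or the contrast, so the two-sided 5% level holds on some readings and not on others

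*Protocol article*

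**What the plan says.** Data management and analysis treats both outcomes as continuous and analyses their change over time with a "two-way mixed effects linear repeated measures analysis of variance (ANOVA"). It names effects within groups, between groups and over time, and gives the last of these the main interest. All analyses are to report 95% confidence intervals and "consider p-values equal to or less than 0.05 (two-tailed) to be significant".

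The time unit has to be pieced together:

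- The Outcomes section defines the primary outcome as mean logins per month per organization within each of the baseline, intervention and crossover periods.
- The Abstract sets the window from baseline to the end of the intervention period, which is two plus six months.
- Statistical precision assumes primary data "at six follow-up points (one per month").
- Data management and analysis allows logins to be averaged over longer spans, such as two months, if counts are low. That makes single months the natural default.

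The only correlation assumption is in Statistical precision, which says that "an estimation of intra-class correlation coefficient (ICC) of measurements for individuals over time for the primary outcome is required", and then: "we calculated estimates of statistical precision for ICCs of 0.2, 0.3, 0.5, 0.7 and 0.8". Those calculations concern a time-averaged difference between arms over the six intervention months.

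**The concern.** A classical two-way mixed repeated measures ANOVA tests within-organization effects, including arm by time, against one pooled within-organization mean square. With more than two time points this is valid only under sphericity: differences between any two months must all have the same variance. For logins to a new service, neighbouring months may well be more alike than distant ones. A contrast of the two earliest months with the six later ones then varies more than the pooled error implies, and the interval for the change is too narrow.

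At stake is whether the primary test keeps its stated 5% level. The claim at risk is that full-serve access increases use. The precision calculation would not reveal the problem, because the quantity behind it is not a change and is tested against between-organization error.

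**Working it through.** **Inputs.** From Statistical precision: "80% power, an estimated standard deviation of 1.0, significance of 0.05 (two-sided test"), and "42 organizations per study group (total n = 85"); the calculations use 42 per arm, N = 84. From the design: 2 baseline months, 6 intervention months, 2 crossover months. **Assumed:** AR(1) correlation between months, ρ = 0.3 to 0.8, with variance 1.

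**Step 1. The plan's own figures.** Detectable difference = (1.960 + 0.842) × √[2(1 + 5 × ICC)/(6 × 42)].

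| ICC | 0.2 | 0.3 | 0.5 | 0.7 | 0.8 |
|---|---|---|---|---|---|
| Computed | 0.353 | 0.395 | 0.467 | 0.529 | 0.558 |
| Stated | 0.35 | 0.39 | 0.47 | 0.53 | 0.56 |

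All reproduce. They describe the time-averaged difference, whose test keeps about 5% under decay (simulated 4.7-6.0%).

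**Step 2. Baseline-versus-intervention contrast on eight monthly values, pooled error.** Let c = (−1/2, −1/2, then 1/6 six times), so c'c = 2/4 + 6/36 = 0.667. Let S be the correlation matrix of the months. The true variance of the contrast is proportional to c'Sc. The ANOVA uses MSW × c'c, where MSW = 1 minus the average correlation over pairs of months. The pooled error has 82 × 7 = 574 degrees of freedom and critical value 1.964. The actual error rate is 2 × P(t > 1.964/√R), with R = c'Sc/(MSW × c'c).

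In full for ρ = 0.5:

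- Variance of the baseline mean: (1 + 0.5)/2 = 0.750.
- Variance of the intervention mean: [6 + 2(5ρ + 4ρ² + 3ρ³ + 2ρ⁴ + ρ⁵)]/36 = 14.0625/36 = 0.391.
- Covariance of the two means: (0.9844 + 0.4922)/12 = 0.123.
- c'Sc = 0.750 + 0.391 − 2 × 0.123 = 0.895.
- MSW = 1 − 0.2146 = 0.785, so the ANOVA uses 0.785 × 0.667 = 0.524.
- R = 0.895/0.524 = 1.71 and √R = 1.31. Error rate = 2 × P(t > 1.50) = 13.3%.

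| ρ | c'Sc | MSW × c'c | True SE / reported SE | Error rate |
|---|---|---|---|---|
| 0.3 | 0.833 | 0.600 | 1.18 | 9.6% |
| 0.5 | 0.895 | 0.524 | 1.31 | 13.3% |
| 0.7 | 0.830 | 0.397 | 1.45 | 17.5% |
| 0.8 | 0.695 | 0.301 | 1.52 | 19.7% |

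Adding a constant organization effect to the AR(1) part changes nothing, because it cancels from both variances. Milder patterns inflate less. An organization effect (0.4), an AR(1) part (0.3) and independent noise (0.3) give about 7-10%. Organization-specific slopes give 6-9%. The plan's fallback of two-month means gives about 6-9% under pure AR(1).

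**Step 3. Omnibus group-by-time test on eight months, simulated with no effect.** Error is 5.7% at ρ = 0.3, 7.3% at 0.5, 8.5% at 0.7 and 9.5% at 0.8. With equal correlations it is about 5%. With a Greenhouse-Geisser correction it is 4.3-5.4% for ρ of 0.5 to 0.9.

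**Step 4. Other readings of the same text.**

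- Two period means (baseline, intervention): exactly 5%, because sphericity is automatic with two levels.
- Three period means with pooled error: R is 0.82 at ρ = 0.5 and 0.73 at ρ = 0.8, so error is 3.0% and 2.2%. The baseline-intervention contrast is conservative.

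**Step 5. One change score per organization, ordinary two-sample t-test.** Simulated error is 4.9-5.2% for every ρ examined.

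**The case against.** The strongest reply is that the text does not commit the trial to the faulty test. The analysis section states no covariance structure, does not say that sphericity will be assumed, and does not rule out a general mixed model, an epsilon correction or a contrast-specific error term. Such details commonly sit in a statistical analysis plan, which is not at hand, and this is a condensed article. The Outcomes section describes period means, and two period means give exactly 5%. The decay is assumed, and the authors themselves say they cannot estimate even the ICC.

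Most of this stands. A reader might infer that the primary analysis uses a single ICC and that its error rate is therefore 10-19%, with an interval that is certainly too narrow. The protocol does not support that. The single ICC belongs to the precision calculation alone, and the higher rates need four things together: monthly values, a one-degree-of-freedom change contrast, pooled error and decaying correlation. Silence on the covariance structure is not held against the article here.

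What does not fall away is that the article names a specific method, makes change its focus and points to months as the default unit, yet never says which comparison is the primary test. An epsilon correction would repair the omnibus test, but not by itself a single contrast on pooled error.

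**Conclusion.** The point holds in conditional form. As worded, the primary analysis permits error rates for the arm comparison of change from about 2-3% (three period means, pooled error), through 5% (two period means), to about 6-10% (omnibus test on months) and about 10-20% (two baseline against six intervention months, pooled error). The two inflated ranges rest on an assumed AR(1) correlation of 0.3 to 0.8 and on an uncorrected pooled error term. They show how sensitive the test is and do not estimate this trial's error rate.

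The time-averaged precision figures are correct for the quantity they describe, but that quantity is not the change that the analysis section puts first. The survey outcome is measured only twice, so the sphericity issue does not arise for it. The gap should be closed before the data are seen. Confidence is medium, because the size depends on a correlation pattern that the protocol does not give.

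**What to change.** State the primary test in one sentence: the arms are compared on one mean for the intervention period (months 3-8) per organization, together with that organization's baseline mean (months 1-2), with variation between organizations as the error term. The baseline mean can join the covariates already planned for the analysis of covariance. With one row per organization, the test holds 5% whatever the correlation between months, and it fits the period-based definition in the Outcomes section.

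Keep the monthly model as secondary, or fit it with an unstructured covariance and small-sample degrees of freedom.

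The cost is a change of analysis wording only, with no new data. The downside is that the monthly pattern of use becomes a secondary display.
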